#### Crossover phase

Participants only enter the crossover phase if they do not meet antidepressant response criteria at the end of the randomized treatment phase. During the crossover phase, ECT non-responders receive a course of 9 or 12 ketamine infusions, while ketamine non-responders undergo 9 or 12 ECT sessions. Non-responders at the end of the crossover phase exit the study. Those meeting the response criteria after the crossover phase (≥ 50% MADRS score decrease relative to pre-crossover score and MADRS score < 22) may enter the maintenance phase.

#### Maintenance phase

Treatment during the maintenance phase lasts 6 months from entry (immediately after completion of the randomized treatment or crossover phase), with a follow-up assessment at month 7. ECT maintenance follows standard of care wherein the treating physician will determine if the participant will receive ECT maintenance, and if so, the frequency of these treatments in accordance with patients’ needs and Canadian Network for Mood and Anxiety Treatments (CANMAT) 2016 Clinical Guidelines [15]. Participants undergoing ketamine maintenance treatment receive infusions according to the following schedule: 1 infusion per week for the first 4 weeks, followed by 1 infusion every 2 weeks for 2 months, and then 1 infusion every month for 3 months. Individuals who experience a relapse of depressive symptoms (MADRS ≥22 or loss of 50% improvement from baseline) with monthly ketamine infusions may return to bi-weekly infusions for the remainder of the maintenance phase. Participants who fail to meet response criteria at any two consecutive study visits during the maintenance phase discontinue treatments (if present) and exit the study. At the conclusion of study participation, all participants have a final follow-up visit and are discharged to their referring physician with treatment recommendations.

### Assessments

#### Clinical platform

Participants in both arms are clinically assessed on an identical schedule. Clinical raters receive standardized training in the administration of measures of interest, and are assessed for inter-rater reliability. They remain blind to treatment arm and are not otherwise involved in the study, while participants are instructed not to disclose their treatment arm during ratings. On visits consisting of both clinical scales and treatment, clinical ratings are administered prior to treatment. Clinical scales are listed in Table 2.

**Table 2 Tab2:** Clinical assessments

*Clinician-Administered Assessments*	
Mini International Neuropsychiatric Interview (MINI)	
Montgomery-Åsberg Depression Rating Scale (MADRS)	
Clinical Global Impression (CGI)	
Young Mania Rating Scale (YMRS)	
Columbia-Suicide Severity Rating Scale (C-SSRS)	
Toronto Side Effects Scale (TSES)	
Montreal Cognitive Assessment (MOCA)	
CNS Vital Signs (CNS-VS), Computerized neurocognitive battery	
*Self-Report Assessments*	
Patient Health Questionnaire (PHQ-9)	
Generalized Anxiety Disorder 7-item scale (GAD-7)	
Quality of Life, Enjoyment and Satisfaction Questionnaire-short form (Q-LESQ-SF)	
Dimensional Anhedonia Rating Scale (DARS)	
Medical Outcome Study - short Form 36 (SF-36)	
Drug Abuse Screening Test (DAST-10)	
Beck Scale for Suicide Ideation (BSS)	

The primary study outcome measure is response rates to randomized treatment determined through percent change in MADRS scores from baseline (pre-randomized treatment phase) to end of randomized treatment. The MADRS is a 10-item scale designed to measure depression severity administered by a blinded rater using the Structured Interview Guide for the Montgomery-Åsberg Depression Rating Scale (SIGMA) [31]. Additional assessments include the Clinical Global Impression, Severity and Improvement Scales (CGI-S and CGI-I) [32], the C-SSRS, and the Young Mania Rating Scale (YMRS) [33]. Clinical assessments are obtained prior to each treatment during the first week (i.e., thrice-weekly), and then at weekly intervals throughout the randomized treatment and crossover phases. When administration of these scales occurs at shorter time intervals than the validated measurement timeframe, symptoms are assessed for the time period since last treatment.

Participants complete electronic self-report measures on the same schedule as the above-listed clinical assessments. These include the Patient Health Questionnaire (PHQ-9) [34], Beck Scale for Suicide Ideation (BSS) [35], General Anxiety Disorder 7-item Scale (GAD-7) [36], Quality of Life, Enjoyment and Satisfaction Questionnaire - Short Form (Q-LESQ-SF) [37], Dimensional Anhedonia Rating Scale (DARS) [38], and Medical Outcome Study - Short Form 36 (SF-36) [39].

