## Methods/design

### Protocol overview

The study design is a multi-centre, prospective, longitudinal, randomized, crossover, non-inferiority trial comparing ECT and IV ketamine infusions (Fig. 1). After being referred for and consenting to ECT, individuals with MDD or BP currently experiencing a MDE are then offered the opportunity to enroll in this study. Participants who consent are randomized to ECT or ketamine by the site coordinator using a computerized randomization sequence stratified by centre with a 1:1 allocation using random block sizes. During the randomized treatment phase, participants receive a course of thrice-weekly ECT or ketamine infusions for 3 or 4 weeks. Non-responders to the first randomized treatment (< 50% reduction in depression severity as assessed by blinded raters using the Montgomery-Åsberg Depression Rating Scale [MADRS] [22], and MADRS score ≥ 22) crossover to receive treatment with the second strategy. Participants continue taking any concomitant medication throughout the study, with no change in medication regimen permitted during the initial randomization or crossover phase. Individuals who achieve response (≥ 50% reduction in MADRS scores and MADRS score < 22) in either the randomized treatment or crossover phase are eligible to enter the maintenance phase, while treatment non-responders following the crossover phase exit the study. During the 6-month maintenance phase, ECT is administered at the discretion of the prescribing physician as per standard of care, while ketamine is administered according to a set schedule. Clinical, cognitive and molecular assessments are conducted at baseline (prior to treatment initiation), post-randomized treatment phase (following weeks 3 or 4), post-crossover phase (if present), and mid- and post-maintenance phase. Neuroimaging occurs at baseline, post-randomized treatment phase, and mid-maintenance (imaging occurs less frequently due to cost and increased participant burden). As part of the CAN-BIND Integrated Discovery Program, this trial is principally funded by the Ontario Brain Institute (OBI). The lead site overseeing the clinical trial is the Royal’s Institute of Mental Health Research (IMHR), affiliated with the University of Ottawa and the Principal Investigator is [name].

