### Data analyses

The primary outcome measure is the rate of antidepressant response (i.e., percentage of participants meeting antidepressant response criteria [≥ 50% reduction in MADRS scores from baseline and MADRS score < 22]) in each arm at the end of the randomized treatment phase. A total of 240 participants will be enrolled into the randomized treatment phase across the four recruiting sites. This will allow for a 20% drop-out rate (i.e., withdrawal of approximately 40 participants), resulting in a total sample of *N* = 200. For the primary efficacy analyses, a non-inferiority margin of 20% was selected based on clinical judgment. Thus, a sample of 200 participants (*N* = 100/treatment arm) is required to be 90% certain that the upper limit of a one-sided 95% confidence interval will exclude a difference in favour of the ECT group of more than 20%. Secondary efficacy outcomes will include percent change in MADRS scores from baseline to the end of the randomized treatment phase, and remission rates (MADRS score ≤ 10). Response and remission rates will also be assessed for the crossover phase. Clinical scores will be analyzed using linear mixed models (appropriate covariates, such as site, will be included, as needed). Categorical outcomes (response/remission) will be examined using χ^2^ tests. The alpha will be set at 0.05.

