Speed of therapeutic effects is defined as the number of treatments required for participants to first meet antidepressant response criteria. A Kaplan-Meier survival analysis will be used to compare the mean number of required treatments for first response to ECT and ketamine during the randomized treatment phase. Side effect burden will be quantified by summing the total frequency and severity scores of the TSES administered after the final treatment during the randomized treatment phase. Mean total TSES scores for ECT and ketamine will be compared using an ANOVA (appropriate covariates will be included). Further, side effect profiles for each treatment will be derived by identifying the most common side effects reported in each arm of the trial (present in > 5% of participants). Treatment tolerability will be estimated via dropout rates. Finally, data from CNS Vital Signs will permit comparison of any cognitive side effects associated with ECT or ketamine (compared at the end of the randomized treatment phase). Level of health care utilization (estimated using average cost of treatment administration, number of days of inpatient hospitalization, and frequency of outpatient consultations) associated with ECT and ketamine will be compared using ANOVAs.

The main outcome in the maintenance phase will be time to relapse. Due to differences in the administration schedules of ECT and ketamine during maintenance, two parallel descriptive statistics will be outlined. For each treatment, mean time to relapse (loss of antidepressant response) will be estimated using Kaplan-Meier survival analysis.

While data from each analytical platform will be analyzed independently using the methods described herein and elsewhere [21], integration of data collected across platforms will also be carried out, and will be overseen by the CAN-BIND Data Science Advisory Team comprised of Principal Investigators, domain-specific informatics advisors, and operations support. In addition to conventional statistical approaches, machine-learning approaches will be applied particularly with regards to outcome prediction (i.e., response/non-response to ECT and ketamine at 3 or 4 weeks of treatment).

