This trial is comparing the efficacy, speed of therapeutic effects, side effect profiles, and health care resource use associated with ketamine and ECT. As a non-inferiority trial, we expect ketamine to exhibit similar efficacy rates as ECT yet with more rapid antidepressant effects, less side effects, and with substantially less cost and health care resource use. This study is among the first to directly compare these treatments using a randomized design, complementing an ongoing, large-scale, parallel-arm clinical trial comparing ketamine and ECT for treatment-resistant depression in the United States (the ELEKT-D trial) [53]. Unique aspects of our trial include the crossover design, where participants who do not respond to the first randomized treatment may crossover to receive treatment with the alternate strategy, longer-term treatment and follow-up through the maintenance phase, and the inclusion of individuals with either unipolar or bipolar depression. Ketamine and ECT are both effective treatments for BP [54, 55], although, the assessment of effective and long-lasting treatments in the context of BP has received substantially less attention than that of unipolar depression.

Another strength of the current study is that both treatment arms are administered under comparable conditions. There is a balanced frequency of treatment administration in each arm during the acute treatment phases. Moreover, ECT and ketamine treatments are administered in the same setting at each site, reducing variability that could arise due to numerous confounding factors. Finally, since treatments cannot be blinded from participants or from clinical and research staff, clinical ratings are being conducted by raters who are blind to the treatment and are otherwise not involved in the trial. This rigorous study design allows for the relatively unbiased evaluation of the antidepressant effects of ketamine relative to an active comparator, addressing a critical gap in this area.

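### Speed is counted in single treatments, but after week 1 response is rated only about every third treatment, so each arm's mean is overstated and the difference in means can be biased either way

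*Protocol article*

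**What the plan says.** All references are to the protocol article.

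- **Outcome (Data analyses):** "Speed of therapeutic effects is defined as the number of treatments required for participants to first meet antidepressant response criteria".
- **Analysis (Data analyses):** "A Kaplan-Meier survival analysis will be used to compare the mean number of required treatments for first response to ECT and ketamine", within the randomized phase. Nothing is said about responses that occur between ratings.
- **Response criterion (Data analyses):** "≥ 50% reduction in MADRS scores from baseline and MADRS score < 22". A response therefore cannot be established without a MADRS score, which Clinical platform assigns to a blinded rater.
- **Rating schedule (Clinical platform):** "Clinical assessments are obtained prior to each treatment during the first week (i.e., thrice-weekly), and then at weekly intervals throughout the randomized treatment". The order on a treatment day is also fixed: "On visits consisting of both clinical scales and treatment, clinical ratings are administered prior to treatment". The two arms do not differ in this: "Participants in both arms are clinically assessed on an identical schedule".
- **Treatment frequency (Protocol overview):** "participants receive a course of thrice-weekly ECT or ketamine infusions for 3 or 4 weeks", which makes 9 or 12 treatments.

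**The concern.** The outcome has a resolution of one treatment. The instrument that defines it has that resolution only in week 1; afterwards it is read about once per three treatments. A participant who first meets the criteria between two weekly ratings is given the later count, and a standard Kaplan-Meier analysis takes that count as the event time. The error goes one way for an individual (late, never early) and is zero for anyone who responds in week 1.

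Speed of effect is named in the primary objective, and the Discussion states that "we expect ketamine to exhibit similar efficacy rates as ECT yet with more rapid antidepressant effects". A reported mean number of treatments to response, and the difference between two such means, would therefore be read closely, while part of both would reflect the visit schedule.

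**Working it through.** The article gives no figure for the speed outcome, so there is nothing to reproduce. The check builds the rating grid from the text and asks what it does to the means.

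**Step 1: the grid.** A rating taken before treatment k+1 shows status after k treatments. In week 1, the ratings before treatments 2 and 3 show status after 1 and 2. If each later weekly rating precedes that week's first treatment, and the phase ends with a rating, the further points are 3, 6, 9 and 12. The article does not state the day of the weekly rating, so this placement is an assumption. Another day would move the points but leave them about three treatments apart.

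**Step 2: recorded count g(t) for true count t.**

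| True t | Recorded g(t) | Delay |
|---|---|---|
| 1, 2, 3 | 1, 2, 3 | 0, 0, 0 |
| 4, 5, 6 | 6 | 2, 1, 0 |
| 7, 8, 9 | 9 | 2, 1, 0 |
| 10, 11, 12 | 12 | 2, 1, 0 |

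If responses are evenly spread within a week, the mean delay after week 1 is (2 + 1 + 0)/3 = 1.0 treatment.

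**Step 3: pairs of participants with different true counts from 1 to 12.** If the earlier one responds in week 1, the recorded gap is larger than the true gap in 18 of 30 pairs, equal in 12 and smaller in none. If both respond after week 1, it is larger in 9 of 36, equal in 9 and smaller in 18 (for example, 4 versus 6 becomes 6 versus 6).

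**Step 4: means.** Let h(t) be the chance of first response at treatment t among those not yet responding, S(t) the proportion still without response after t, and f(t) = S(t−1)·h(t). The restricted mean over 12 treatments is Σ t·f(t) + 12·S(12). Replacing t by g(t) adds

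excess = 2f(4) + f(5) + 2f(7) + f(8) + 2f(10) + f(11).

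This is never negative, so each arm's mean is overstated whenever responses fall between weekly ratings. The bias in the difference (slower minus faster arm) is the slower arm's excess minus the faster arm's excess.

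The article gives no hazards. Those below are assumptions chosen to span different timing patterns.

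*Faster arm early, slower arm late.* Faster: h = 0.25 in week 1, then 0.05. Slower: h = 0.02 in week 1, then 0.15.
- Faster excess: 2(0.0211) + 0.0200 + 2(0.0181) + 0.0172 + 2(0.0155) + 0.0147 = 0.16.
- Slower excess: 2(0.1412) + 0.1200 + 2(0.0867) + 0.0737 + 2(0.0532) + 0.0453 = 0.80.
- Bias: 0.80 − 0.16 = +0.64.

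*Both arms only after week 1.* h = 0 in week 1, then 0.25 (faster) or 0.12 (slower).
- Faster excess: 2(0.2500) + 0.1875 + 2(0.1055) + 0.0791 + 2(0.0445) + 0.0334 = 1.10.
- Slower excess: 2(0.1200) + 0.1056 + 2(0.0818) + 0.0720 + 2(0.0557) + 0.0490 = 0.74.
- Bias: 0.74 − 1.10 = −0.36.

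| Assumed pattern (faster; slower) | True difference | Recorded difference | Bias |
|---|---|---|---|
| Early; late | 2.33 | 2.97 | +0.64 |
| Constant 0.25; 0.10 | 3.30 | 3.32 | +0.01 (before rounding) |
| Constant 0.15; 0.08 | 2.19 | 2.10 | −0.09 |
| Both after week 1: 0.25; 0.12 | 2.00 | 1.64 | −0.36 |

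Restricting to 9 treatments gives the same picture: 2.30 to 2.83, 2.43 to 2.38, 1.48 to 1.38, and 1.18 to 0.78.

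**Step 5: no true difference.** If both arms have the same f(t), the two excesses are equal and the recorded difference is zero.

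**The case against.** The strongest counter-argument is that both arms share one rating schedule. That stands in part: as Step 5 shows, the grid cannot create a difference where there is none. It can only stretch or compress a real one.

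A reader might infer more, namely that the schedule inflates ketamine's speed advantage. The document does not support this as a general statement. It expects faster ketamine effects, and its Background describes response within hours of a single infusion, so an upward bias is possible. The same Background also reports response rates that rise with repeated infusions, so some first responses to ketamine would fall after week 1 and be recorded late too. No split of responses by week is given for either arm. A fixed percentage inflation can be obtained by giving both arms the same week-1 mean and the same later spread, but that percentage is set by the assumptions, not by the trial.

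It can also be said that treating staff assess response at every treatment visit. The article does not say that this is a MADRS rating, and it states that treatment cannot be blinded from clinical staff, so those checks do not fill the gap without giving up the blinded outcome.

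Finally, a full analysis plan may deal with event times between visits, and with complete ratings the Kaplan-Meier proportions at the rated points already equal the interval-censored ones. Both remarks are fair and limit the point. The article nonetheless names the summary to be compared, a mean count of treatments, and that summary is the part the grid distorts.

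**Conclusion.** The point holds as a loss of resolution with a bias of unknown sign. After week 1, first responses are recorded 0 to 2 treatments late, about 1 on average if evenly spread. Each arm's mean is overstated. The difference in means is biased upward if one arm responds mainly in week 1 and the other later (+0.64 of a treatment in the example), is nearly unbiased under constant hazards (+0.01 and −0.09), and is biased downward if both respond mainly after week 1 (−0.36).

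These sizes rest on assumed hazards, complete ratings and follow-up to 12 treatments, and on the weekly rating preceding the week's first treatment. The direction in this trial cannot be known beforehand from the document.

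The point is minor. Speed appears in the primary objective, but the primary outcome is the response rate, and neither the sample size nor the non-inferiority conclusion depends on the speed analysis.

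**What to change.** In Data analyses, define first response as lying between the last rating without response and the first rating with it. Analyse it as interval-censored, or with a discrete-time model on the rating grid common to both arms. Report the cumulative proportion responding by arm at each rated point (after 1, 2, 3, 6, 9 and 12 treatments, or the actual points if the weekly rating falls on another day), and state which day that is. Do not present a mean number of treatments as an exact count.

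No additional ratings and no change to treatment are needed; the cost is analysis wording. The downside is that speed is then stated only at visit resolution.

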#### Cognitive assessment

A computerized neurocognitive test battery is administered prior to treatment initiation and at the completion of each treatment phase (Fig. 1). CNS Vital Signs [40] is a battery comprised of well-established cognitive tests including verbal and visual memory, finger tapping, symbol digit coding, Stroop Test, a test of shifting attention, and continuous performance test. Cognitive testing is being used to assess and compare potential effects of repeated ECT and ketamine treatment on cognitive function, and as a possible marker of response prediction.

#### Neuroimaging platform

Structural and functional neuroimaging data are acquired at each participating site using a 3 T MRI scanner. Among the four sites, the following scanners are used: Siemens Biograph mMR PET/MR (Ottawa), 3 T Siemens Trio (Kingston) and Siemens Prisma 3 T (Toronto and Montreal). Extensive initial and ongoing standardization and quality control procedures have been implemented to ensure that comparable and high-quality data are acquired across sites [41]. Specifically, all sites are using either identical or comparable scanning protocols, identical participant instructions and consistent standard operating procedures (SOPs) in keeping with existing CAN-BIND imaging protocols [42]. Each site carries out quarterly scanning using the fBIRN phantom, a spherical agar phantom developed by the ‘functional Brain Imaging Research Network’ consortium [43].

Each participant undergoes 2 or 3 imaging sessions: 1) at baseline, prior to treatment initiation, 2) after 3 or 4 weeks of randomized treatment, and 3) for responders, at the mid-point of maintenance (after approximately 4 consecutive months of treatment). During each session, structural MRI, resting-state functional MRI (rs-fMRI), and diffusion tensor imaging (DTI) data are acquired, consistent with established CAN-BIND imaging protocols [42]. In brief, a T1 scan is first acquired (TR = 1760 ms, TE = 2.19 ms, slice thickness = 1 mm, FOV = 256 mm, flip angle = 15, sagittal acquisition, GRAPPA on); a T2-weighted BOLD EPI scan is then obtained while participants look at a fixation cross (TR = 2500 ms, TE = 30 ms, slice thickness = 3 mm, FOV = 210 mm, flip angle = 83, GRAPPA on, acceleration factor PE = 2, acquisition: interleaved). This is followed by DTI acquisition (TR = 8000 ms, TE = 94 ms, GRAPPA: on, acceleration factor PE = 2, 30 directions at 2 b-values:1 and 1000 s/mm^2^; monopolar diffusion, voxel size: 2.5mm^3^, 58 slices, orientation: transverse, FOV = 240 mm). An additional multi-echo magnetization prepared-rapid gradient echo (ME-MPRAGE) sequence has been added to the CAN-BIND imaging protocol across most sites for higher resolution structural images (TR = 1760 ms, TE1/2/3/4 = 1.69/3.55/5.41/7.27 ms, slice thickness = 1 mm, FOV = 256 mm, flip angle = 7, sagittal acquisition, GRAPPA on, acceleration factor PE = 2). Finally, at the Ottawa and Montreal sites, proton magnetic resonance spectroscopy (^1^H-MRS) data are acquired from the dorsal anterior cingulate cortex to measure glutamate + glutamine (Glx) (Point RESolved Spectroscopy [PRESS]; TR = 2000 ms, TE = 30 ms; voxel, water suppression BW: 70 Hz, averages: 128, 40 × 20 × 15 mm). Neuroimaging is being conducted to identify potential predictors of response and non-response, and examine changes in brain features with acute and longer-term treatment.

